# Preventing sickness absenteeism among employees with common mental disorders or stress-related symptoms at work: Design of a cluster randomized controlled trial of a problem-solving based intervention versus care-as-usual conducted at the Occupational Health Services

**DOI:** 10.1186/s12889-017-4329-1

**Published:** 2017-05-12

**Keywords:** Common mental disorders, Cluster randomized study, Stress-related disorders, Adjustment disorders, Depression, Exhaustion, Work environment, Occupational health services, Participative methodology, Problem solving therapy

## Abstract

**Background:**

Common mental disorders (CMDs) are among the leading causes of sick leave in Sweden and other OECD countries. They result in suffering for the individual and considerable financial costs for the employer and for society at large. The occupational health service (OHS) can offer interventions in which both the individual and the work situation are taken into account. The aim of this paper is to describe the design of a study evaluating the effectiveness of an intervention given at the OHS to employees with CMDs or stress-related symptoms at work. In addition, intervention fidelity and its relation to the outcome will be assessed in a process analysis.

**Methods:**

The study is designed as a cluster randomized trial in which the participating OHS consultants are randomized into either delivering the intervention or performing care as usual. Employees with CMDs or stress-related symptoms at work are recruited consecutively by the OHS consultants. The intervention aims to improve the match between the employee and the job situation. Interviews are held individually with the employee and the nearest supervisor, after which a joint meeting with both the employee and the supervisor takes place. A participatory approach is applied by which the supervisor and the employee are guided by the OHS consultant and encouraged to actively take part in problem solving concerning the work situation. Outcomes will be assessed at baseline and at six and 12 months. A long-term follow-up at 3 years will also be performed. The primary outcome is registered sickness absence during a 1-year period after study inclusion. Secondary outcomes are mental health and work ability. The intervention’s cost effectiveness, compared to treatment as usual, both for society and for the employer will be evaluated. A process evaluation by both the OHS consultants and the employee will be carried out.

**Discussion:**

The study includes analyses of the effectiveness of the intervention (clinical and economic) as well as an analysis of its implementation at the participating OHSs. Possible methodological challenges such as selection bias and risk of contamination between OHS consultants delivering the experimental condition and consultants giving usual care are discussed.

**Trial registration:**

ClinicalTrials NCT02563743 Sep 28 2015.

## Background

Common mental disorders (CMDs) usually include depression, anxiety and adjustment disorders. They are the leading cause of all sick leave lasting for more than 14 days in Sweden [1] as well as being highly prevalent in several other OECD countries [2]. In Sweden, 50 % of all newly granted disability benefits awarded to women in December 2015 were due to mental health problems; the figure for men was 37% [1].

It has been estimated that the cost of mental health problems amounts to approximately €136 billion per year in Europe [3]. For the afflicted individual, mental health problems give rise to considerable suffering and, in the long run, an increased risk of social isolation and a substantial deterioration in personal finances. Furthermore, people on long-term sick leave for mental health problems have an increased risk of mortality from suicide or diseases such as cardiovascular diseases and cancer [4].

Recent systematic reviews have found that work-environment factors such as high job demands combined with low levels of control at work increase the risk of mental health problems [5, 6]. Other work-environment factors that heighten the risk of CMDs include low social support, job insecurity and an imbalance between work effort and the reward or recognition that the work receives. The risk of future mental health problems is lower among employees who believe that they are treated fairly at work and are able to influence their work [5]. Several calls for further intervention research within this area have been made [7, 8].

Interventions aimed at preventing or reducing work-related mental health problems can be conducted at the organizational, work group or individual level or combinations of these levels. Interventions aiming at return to work (RTW) or the reduction of sick leave evaluated in randomized controlled trials (RCTs) are often conducted at the individual level without actively including the workplace [9]. Individuals on sick leave due to CMDs, and for whom a change in their work situation is important, may hence risk new periods of sick leave and continued mental health problems if the workplace is not involved. Indeed, recent research suggests that adding a workplace-focused approach to a clinical intervention is effective in improving work return among employees suffering from depression [10]. Furthermore, studies evaluating workplace-focused interventions for mental health problems have found some support for an improvement in RTW among employees receiving problem-solving therapy (PST) [11, 12] or cognitive behavioural therapy (CBT) [13].

Interventions for improving RTW, such as PST or workplace-focused measures aimed at improving workability among employees [14, 15] may also be effective in preventing sickness absenteeism among employees with mild mental problems or occupational stress who continue to work but are at risk of future sick leave. A study by Lexis et al. [16] evaluated an intervention based on CBT and PST techniques among bank personnel who were not on sick leave but had mild to severe depression. The control group received care as usual consisting of a consultation with an occupational physician. The results showed a statistically significant lower total amount of sickness absenteeism, and a lower proportion of depressive symptoms among the intervention group compared to the control group after 12 months. Other published studies of early interventions among employees at risk of future mental health problems, reduced work functioning and/or sick leave have produced varying results (e.g [17–21]).

The occupational health service (OHS) has knowledge of the employee’s work environment and can offer interventions to prevent sickness absenteeism which take both the individual and the work situation into account. To the best of our knowledge, this is the first RCT of an intervention for employees with stress-related symptoms or CMDs conducted in a Swedish OHS setting.

The aim of this paper is to describe the design of a study which evaluates an individually- and workplace-focused intervention given at the OHS to employees with CMDs or stress-related symptoms at work. In particular, the intervention’s impact on sick leave and mental health as well as its cost-effectiveness will be studied. Furthermore, a process evaluation will be conducted to assess intervention fidelity and its association with future sick leave.

## Methods

### Study design and setting

The study has a two-armed cluster randomized controlled design with a primary follow-up period of 1 year (see Fig. 1). The study is conducted in collaboration with three OHSs in Sweden. One OHS has nationwide coverage while two are regional OHSs. Each participating OHS consultant is considered as one cluster. The participating OHS consultants consist of occupational nurses, physicians, physiotherapists, ergonomists, occupational health counselors and psychologists.

**Fig. 1 Fig1:**
[figure not shown]
Study design and overview of the trial

### Ethical approval

Ethical approval has been granted by the Ethical Review Board in Stockholm (registration number 2015/549–31/1). The study complies with the ethical guidelines regarding voluntary participation, privacy and the handling of personal data in accordance with Sweden’s Personal Data Act and Secrecy Act. Informed consent will be obtained from all participants and will include, amongst other things, information about the right to opt-out from the study at any time without giving a reason and without any consequence for the help received from the OHS (see also Recruitment of participants).

### Recruitment of participants

The OHS consultants provide preliminary information about the study to employees seeking care at the OHS for work-related stress symptoms or CMDs which fulfil the inclusion criteria. They then ask whether the employee’s contact information may be sent to the research group at Karolinska Institutet (KI). Written consent to transfer this information to KI is obtained from those who are preliminarily interested in participating in the study. Subsequently, members of the research group contact the employee and give both verbal and written information (sent by email) about the study and what participation would entail. Final consent is obtained and study inclusion achieved when the employee has submitted the baseline questionnaire and confirmed having taken part of the information about the study by ticking a box at the end of the baseline questionnaire. Paper-and-pencil questionnaires are offered to those who prefer this option. Recruitment of participants began in September 2015 and will be completed during the spring 2017.

### Inclusion criteria

Inclusion criteria are met by employees fulfilling the following criteria:The employee seeks help at the OHS for occupational stress affecting their ability to work. If the employee is on sick leave due to adjustment disorders, anxiety or depression, the period of sick leave should not have exceeded 3 months at the time of the first OHS visit.The employee should accept involvement of the supervisor in the intervention.The employee also needs to understand both written and spoken Swedish as the study questionnaires and text messages are in Swedish.

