### Blinding

The employees are not given information about the possibility of receiving another type of treatment within the trial. This is because the OHS consultants have been pre-randomized into delivering one of the two interventions. The researchers will not know about treatment allocation during the analyses. However, the OHS consultants are not blinded with regard to which treatment is given.

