**Fig. 2 Fig2:**
[figure not shown]
Overview of the intervention

The interview with the employee’s supervisor covers any earlier measures taken by the employer for the employee and the supervisor’s view of the “causes” of the employee’s stress or poor mental health. The supervisor is also asked about what he/she considers to be the most important problem to address to promote the employee’s work ability or RTW. For practical reasons this meeting usually takes place over the phone and lasts about 15 to 30 min. The same themes are discussed during the interview which takes place in person between the OHS consultant and the employee. However, this session is more comprehensive and also includes an initial section concerning the private situation of the employee, work-family balance, and a survey of possible mismatches between the employee and the job situation [23]. A problem-solving approach is also initiated. This interview takes approximately 90 min.

The problem-solving approach is guided by the following steps (1) goal setting and problem definition – the problem is specified in detail including when and where it happens as well as how it is expressed, (2) generation of possible solutions, (3) decision making about solutions, including potential consequences of different solutions, (4) setting up an action plan, including implementation of prioritized solutions.

During a third meeting the supervisor, employee and the OHS consultant meet face-to-face and focus on problem definition and possible solutions for promoting work ability or RTW. At this meeting the supervisor’s and the employee’s views of the problem are discussed with the aim of achieving a convergence of views. Relevant external parties such as an OHS physician or a representative of the Social Insurance Agency may also participate in this meeting if deemed necessary. The main task of the OHS consultant during the third meeting is to help the employee and his/her supervisor to reach specific problem definitions and feasible solution(s) to be implemented at the workplace to improve work ability or facilitate RTW. The suggested solutions and their follow-up are registered in an action plan by the OHS consultant. It is crucial that both the employee and the supervisor are encouraged to understand, and to be active and participatory in, the problem-solving process and that consensus between the parties is reached on possible solutions to facilitate RTW or manage stress at the workplace.

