### Care as usual

The OHS consultants delivering the control condition receive information about the recruitment process followed by a general introduction to research into psychosocial factors and mental health at work. In total this takes 2 h.

The OHS consultants then continue to deliver the routine care throughout the study period. At the three OHSs where the current study is being performed, care as usual in case of stress-related symptoms and CMDs usually involves both the employee and the supervisor. However, these practices do not follow the same structure as in the experimental intervention nor do they use the mismatch model as guidance for defining problem areas or the described problem-solving approach. At one of the OHSs the intervention is more focused on further medical and lifestyle factors, even though the work situation is also addressed and the employer is involved in the intervention. There is also some variance among the OHS consultants as to how this intervention is applied. One of the OHSs does not usually hold an individual interview with the employee; in other words, the joint meeting between the employee, the employer and the OHS consultant is often held directly after a short interview with the supervisor. A third OHS is about to implement the Swedish guidelines for OHSs concerning the management of mental health at work. These guidelines recommend the involvement of the employer and problem-solving techniques. However, despite the similarities with the experimental intervention the personnel delivering the care as usual have not received the same training in these methods as the consultants delivering the active intervention. A survey of the OHS consultants regarding more specific details of the contents and routines of care as usual will also be conducted as part of the study’s process analysis.

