#### Prognostic measures

The demand-control-support model [39] will be considered as a possible prognostic measure in this study. The study will also include items from the General Nordic Questionnaire (QPSNordic) relating to ongoing conflicts with the superior, perceived loss of control over work tasks and conflicts between the employee’s values and how the work is actually carried out [40]. One self-efficacy item about how confident participants are about whether they will be back to their usual working hours in their usual work position 3 months after the baseline measurement will be developed and validated within the project. Finally, the OHS consultants will be asked a similar question about whether the employee will be back to his/her usual working hours in 3 months’ time.

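### The supervisor-acceptance criterion does not fix the same involvement for both arms and is first applied by unblinded consultants after allocation, so selection on supervisor relations can differ by arm

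*Protocol article*

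**What the plan says.** Under Inclusion criteria, one sentence covers both arms: "The employee should accept involvement of the supervisor in the intervention". The involvement to be accepted is not described further.

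Under Recruitment of participants, the first contact lies with the clusters themselves: "The OHS consultants provide preliminary information about the study to employees seeking care at the OHS". The research group contacts interested employees afterwards and explains participation. Inclusion is complete when the baseline questionnaire has been submitted.

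Under Blinding, allocation comes before recruitment, since "the OHS consultants have been pre-randomized into delivering one of the two interventions". The article adds that "the OHS consultants are not blinded with regard to which treatment is given" and, of the participants, that "The employees are not given information about the possibility of receiving another type of treatment within the trial".

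Under The individual and workplace-focused intervention, the experimental arm has a supervisor interview and then a joint session: "During a third meeting the supervisor, employee and the OHS consultant meet face-to-face". At least three follow-ups with supervisor and employee are recommended over the next 3 months.

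Under Care as usual, the supervisor is as a rule also involved, but "these practices do not follow the same structure as in the experimental intervention".

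Under Prognostic measures, the items to be collected include "ongoing conflicts with the superior, perceived loss of control over work tasks".

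**The concern.** An employee who hears nothing of the other arm can accept or refuse only the supervisor involvement that their own consultant puts to them. If that is more structured and intensive in one arm, the same employee, for example one in conflict with the supervisor, could decline in one arm and accept in the other. The eligibility rule itself would then act differently by arm, after randomisation and before inclusion.

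Randomising consultants does not protect against this, because the employees are selected later. Intention-to-treat analysis does not either, because it starts from those included. The protocol treats conflict with the superior as potentially prognostic, so an arm difference on it could enter the primary comparison of registered absence days.

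**Working it through.** **1. Does the text define one test for both arms?** The article calls both conditions interventions under Blinding and uses the same word for usual care under Care as usual. There are two main readings.
- The criterion refers to each arm's own treatment. Employees are then asked to accept different things.
- The criterion refers to the experimental treatment in both arms. Control consultants must then screen on a procedure they were not trained in, for employees who will not receive it.

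A generic reading (any supervisor involvement) is also possible, but the article does not state a minimum. No reading gives a defined test that is shown to be identical in both arms.

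**2. How far apart are the arms?** Experimental: supervisor interview, face-to-face three-party meeting, and recommended follow-ups. Usual care: supervisor normally involved, different structure, no mismatch model and no such problem-solving approach. At one OHS a joint meeting often follows directly on a short supervisor interview. The contrast is one of degree.

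**3. Do the safeguards reach it?** Methodological considerations asks consultants to inform every employee who meets the inclusion criteria. That presupposes the criterion, so full compliance leaves any arm-dependence in place. Data analysis adjusts only for factors seen to be unevenly distributed and expected to matter. With 75 per arm, an assumed 20% versus 10% gives, ignoring clustering:
- SE = √(0.15 × 0.85 × 2/75) = 0.0583
- z = 0.10/0.0583 = 1.71, two-sided p about 0.09

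An imbalance of that size could be judged acceptable and left unadjusted.

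**4. The plan's own precision.** Inputs from Statistical power: 75 per arm, mean cluster size 5, ICC 0.010, coefficient of variation 0.650, SD 50, difference 25 days, two-sided 0.05, subject-based degrees of freedom (148).
- Design effect = 1 + ((1 + 0.65²) × 5 − 1) × 0.01 = 1.0611
- SE of the difference = 50 × √(2 × 1.0611/75) = 8.41 days
- Noncentrality = 25/8.41 = 2.97, giving power 83.97%, which reproduces the stated 84%

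**5. Illustrative size.** The article gives neither the share of employees with poor supervisor relations nor their excess absence. Both are assumptions here.

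Bias = (difference between arms in share) × (difference in mean days). The type I error is Φ(−1.96 + b/8.41) + Φ(−1.96 − b/8.41), where b is the bias.

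| Imbalance in share | Difference in days | Bias (days) | % of 25 days | Type I error |
|---|---|---|---|---|
| 0 points | any | 0 | 0% | 5.0% |
| 5 points | 10 to 50 | 0.5 to 2.5 | 2 to 10% | 5.04 to 6.0% |
| 10 points | 10 to 60 | 1 to 6 | 4 to 24% | 5.2 to 11.0% |
| 20 points | 10 to 50 | 2 to 10 | 8 to 40% | 5.7 to 22.1% |

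The sign is open: reversing either difference reverses the direction of the bias.

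**The case against.** The strongest reply is that the criterion is one rule for both arms and asks only for acceptance of supervisor involvement, which both arms normally include. Employer involvement features in the account of usual care at each of the three OHSs: as existing practice at two, and at the third through guidelines about to be implemented. Methodological considerations says that both conditions give active workplace-focused treatment. Differences between OHSs are not differences between arms, because randomisation is stratified by OHS unit. The follow-ups are only recommended, may be by phone, and are not stated as something to accept at entry.

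There are also safeguards. Telephone follow-ups in both arms clarify the inclusion criteria, check-lists cover recruitment, the research group explains participation before final consent, victims of workplace bullying are excluded in both arms, and selection by consultants is openly disclosed. Conflict with the superior is measured, so imbalance can be looked for.

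Much of this stands. A reader might infer that the arms are in fact filtered differently and that the result is biased toward the intervention. The article does not support that. It reports no refusals and no imbalance, gives no sign or size for the conflict item, and does not say that supervisor conflict is the channel through which the intervention works. If employees in conflict gain most from the intervention, losing them from that arm would weaken the observed effect.

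What the reply does not remove is the mechanism. Unblinded, pre-allocated consultants apply an undefined acceptance test to offers that differ in structure and intensity. None of the listed safeguards is directed at employees lost through the criterion itself. A condensed article may leave operational detail to the full protocol, but the wording it does fix leaves the arms unaligned.

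**Conclusion.** The concern holds as a risk of differential selection after allocation. The criterion does not set the same supervisor involvement for both arms and is first applied by consultants who know their arm. Whether any imbalance arises, in which direction and how large, cannot be determined from the article.

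On the assumed range, a 10-point imbalance shifts the comparison by about 1 to 6 days (4 to 24% of the 25-day target). Smaller imbalances matter little, and with none there is no bias. The point is worth acting on because the remedy is cheap and the existing adjustment rule is triggered only by a visible imbalance. It does not show that the trial's result will be biased.

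**What to change.** 1. Pre-specify the QPSNordic item on conflict with the superior as a covariate in the primary model, whatever its observed balance. The article does not state when this item is asked; I assume it is in the baseline questionnaire. The cost is one already-planned variable. It corrects only for what that item captures.
2. For employees still to be enrolled, define the supervisor involvement to be accepted identically for both arms. Have the research group confirm it in the same words during the contact it already makes before inclusion, and log refusals by arm.
3. In the check-lists already planned for consultants in both arms after recruitment, ask how many employees were ruled out or declined because of supervisor involvement, and report this by arm.

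There are downsides. A few control employees may become ineligible, and late enrollees would face a slightly different criterion. The consultants' first approach stays unblinded. Recruitment was due to end in spring 2017, so item 2 may help few participants or none; items 1 and 3 remain available after recruitment closes, item 1 provided it is fixed before the outcome analysis.
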